### Eligibility criteria and recruitment

Different community organisations working with multi-ethnic OAs (eg, Asian community, African community) in Swansea will be contacted to request permission to recruit participants through their contacts and members. Local coordinators and sub-coordinators will be approached as they serve as gatekeepers to the recruitment of these OAs. Additionally, recruitment will be done via the sport, play and community networks of the city and county of Swansea, as well as advertising throughout the university where the researchers are located, using the intranet. Recruitment posters/leaflets, letters and email will be used for advertising the study.

Older individuals who are interested will be asked to contact the area project coordinator in their region to express their interest. The researcher will then contact interested participants. Those who are willing to participate will receive a study information sheet. The lead researcher will schedule a mutually agreeable time to meet with them and discuss the study process and procedures with them. If the OA is satisfied to proceed, they will be provided with a consent form to take part in the study.

We will employ a non-consecutive eligibility approach to recruit 20–25 participants from community organisations, which has been identified as a large enough sample to assess the feasibility of the intervention.^3157 82^,^85^ Eligible OAs aged ≥65 years, either male or female, sedentary (self-reported ≥5 total leisure hours sitting per day) and able to communicate in English or Urdu will be included. OAs with physical impairments that hinder them from participating in daily light-intensity PA, those who are currently engaged in daily MVPA (>150 minutes/week) or those who have participated in the past 3 months in a study promoting PA or reducing SB will be excluded. OAs with mental impairment, who are unable to provide informed consent or are unable to cooperate with the research team for the full duration of the project will not be included.

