### Data collection

Pre-intervention and post-intervention measures of PA, SB, self-efficacy, self-report habits and well-being will be completed by participants. Socio-demographic characteristics of OAs will be measured at baseline. A qualitative interview will also be conducted using a semi-structured interview guide after the post-assessment period to assess the acceptability of the intervention. Interviews will be conducted in Urdu or English, with those that are conducted in Urdu translated into English by the primary researcher who will conduct these interviews.

PA will be measured with a wrist-worn accelerometer (ActiGraph wGT9X Link+, Pensacola, Florida, USA). The ActiGraph is reliable^86 87^ and valid for use with OAs,^88 89^ people with mobility limitations^89^ and obese adults.^90^,^92^ To measure each OA’s PA, they will wear the device on their non-dominant wrist for 7 days during waking hours and will remove it during any water-related activities such as bathing or swimming.^93^,^95^

OAs will be given a log sheet and asked to keep track of the times the accelerometer was worn and was removed throughout the day, describing the timings and reasons for each removal.^94 96 97^ Moreover, each OA will receive instructions on how to attach and wear the device for 7 consecutive days. They will also be asked to maintain a sleep log, recording hours slept and waking and rising times. This approach is beneficial to differentiate between wear and non-wear time and it also encourages compliance by acting as a reminder.^98^,^100^ Accelerometer data will be processed using ActiLife V.6.8.0 with data captured in 60 s epochs with the low-frequency extension enabled. The downloaded data will be subjected to compliance and quality control checks, and log sheets will be assessed to check the accuracy of wear time algorithms and to remove the non-wear time from the study.^96^

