### Feasibility assessment

The primary outcome is the acceptability and feasibility of the procedures of the intervention and recruitment and retention measurement. Recruitment rates were determined as the ratio of study participants who consented to participate out of those invited and eligible to participate. We will assess the attendance at, and time taken (minutes) for, the face-to-face health coaching session. Similarly, we will note the number of sent and successfully delivered messages and record the number of responses to, and acknowledgements of, the messages. Further, weekly reading/usage of the pamphlet will be recorded. We will use qualitative interviews to determine their overall user experience with the intervention which will help us to assess device feasibility by examining their perception regarding the vibrations and sound messages emitted from the device.

In addition, we will record drop-out reasons for discontinuing study participants, as well as adverse events experienced (eg, hospitalisation, life-threatening events, death). The suitability of measurement procedures will be evaluated based on the completion rates of the measures.

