### Semi-structured interviews

Following the completion of the intervention, semi-structured interviews will be conducted with enrolled OAs who participated in the trial to understand the intervention’s feasibility and acceptability. The interview guide is based on the UK MRC framework. A key component in planning health-associated interventions is the feasibility phase, which produces important information on areas such as acceptability, usability and functionality that will be assessed using the interview guide (online supplemental file 2).

Interviews will be held either face-to-face or via telephone, Zoom or any other appropriate interface to which the participants have access and will be conducted by the primary researcher ([name]). Enrolled OAs will be interviewed to explore information about the participants’ overall experiences (acceptability, usability and functionality) of using the multi-component intervention and its impact on their PA and SB, any problems they encountered during the intervention and how they feel it could be improved. All interviews are expected to last between 40 and 60 min and will be audio-recorded to allow subsequent verbatim transcription. If interviews are conducted in Urdu, they will be translated into English by the primary researcher ([name]). The reporting of the study will be in accordance with the COREQ checklist to ensure transparent and comprehensive reporting of qualitative research. The checklist is appended in online supplemental file 3, detailing specific items related to the research team, study design and data analysis.

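### The acceptability interview is timed after post-assessment with no interview at withdrawal, so a primary outcome is liable to lean towards completers

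*Protocol article*

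**What the plan says.** Feasibility assessment defines the main endpoint: "The primary outcome is the acceptability and feasibility of the procedures of the intervention and recruitment and retention measurement". The same section assesses the feasibility of the device through interviews about participants' perception of its vibrations and sound messages.

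Two sections fix when the interview happens:

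- Data collection: "A qualitative interview will also be conducted using a semi-structured interview guide after the post-assessment period". Its stated purpose is acceptability.
- Semi-structured interviews: "Following the completion of the intervention, semi-structured interviews will be conducted with enrolled OAs who participated in the trial". Face-to-face, telephone and video modes are all allowed.

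For people who leave, Feasibility assessment says: "we will record drop-out reasons for discontinuing study participants, as well as adverse events experienced". It also lists coaching attendance and duration, message delivery and responses, weekly pamphlet use and completion of the measures.

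Eligibility criteria and recruitment contains a sentence that bears on who can enter and be counted. It begins "OAs with mental impairment, who are unable to provide informed consent or are unable to cooperate with the research team for the full duration", and its closing words are "unable to cooperate with the research team for the full duration of the project will not be included". The recruitment rate is "the ratio of study participants who consented to participate out of those invited and eligible to participate".

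**The concern.** A feasibility study of a new neck-worn device needs to hear from people who gave it up. Someone who stops because the alerts are intrusive or the device is uncomfortable is one of the best informants on acceptability. The stated timing puts the interview at a point that such a person may never reach.

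The interview also carries much of the weight for the device. Feasibility assessment lists no measure of device wear. Study intervention describes the device as standalone and switched off by the participant when not needed. The board has an SD card slot, but the article does not say that wear is logged or analysed. Attendance, message responses and pamphlet use describe the other components and do not explain why a device was abandoned.

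The Abstract says the findings will determine whether a future effectiveness trial is suitable. If the interviewed group is mostly completers, that decision and any redesign of the device rest on the more favourable part of the sample. The limitations listed after the Abstract and in the Discussion cover self-report, the lack of a control group and of follow-up, and the researcher's dual role. They do not mention this selection.

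**Working it through.** The article gives no expected drop-out, retention or acceptability rate, so there is no planned figure to reproduce. The check is a reading of the text, followed by an illustration on assumed rates.

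**1. Timing against population.** Data collection places the interview "after the post-assessment period to assess the acceptability of the intervention". Semi-structured interviews places it after the intervention ends. The same section describes the interviewees as enrolled participants, not as completers. So the population wording is open, while both timing statements point to the end of the study.

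**2. Following one withdrawal through the plan.** Take a participant who stops part-way through the 12 weeks because of the alerts.

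- The reason for leaving is recorded.
- Attendance, message and pamphlet data up to that point may exist.
- No interview is scheduled at withdrawal.
- An interview would happen only if the participant were approached again, or agreed to be, at the end of a study already left. The article does not say that this will be done.

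**3. How many voices could be missing.** Inputs: n = 20 to 25 (Study design overview); drop-out d is assumed. Number not interviewed = d × n, if no one who withdraws is interviewed.

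| Assumed d | n = 20 | n = 25 |
|---|---|---|
| 10% | 2 | 2.5 |
| 20% | 4 | 5 |
| 30% | 6 | 7.5 |

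**4. Scale of a possible lean.** Suppose acceptability were summarised as a proportion, a_c in completers and a_d in those who leave. Then:

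- all enrolled = a_c(1 − d) + a_d·d
- completers minus all enrolled = d(a_c − a_d)

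With a_c = 90% assumed:

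- d = 10%, a_d = 60%: all enrolled = 0.90 × 0.90 + 0.60 × 0.10 = 0.87; difference 3 points.
- d = 20%, a_d = 30%: 0.90 × 0.80 + 0.30 × 0.20 = 0.78; difference 12 points.
- d = 30%, a_d = 30%: 0.90 × 0.70 + 0.30 × 0.30 = 0.72; difference 18 points.
- a_d = a_c, or everyone who leaves is interviewed: difference 0.

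Across drop-out of 10–30% and acceptability of 30–60% in those who leave, the range is 3 to 18 points. This only shows scale. Data analysis specifies thematic analysis, and no acceptability rate is defined. In practice the loss would be of themes and their balance, not of percentage points.

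**5. The eligibility sentence.** It can be read in two ways.

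- As one criterion: the clause after the comma describes people with mental impairment, which makes it a capacity criterion. This is the natural reading.
- As separate grounds: anyone unable to cooperate for the full duration is excluded.

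Under the second reading, people removed on that ground enter neither the retention denominator (they are not enrolled) nor the recruitment denominator (they are not eligible). The article does not state that they will be counted.

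**The case against.** The strongest reply is that the article never restricts interviews to completers. It refers to enrolled participants, includes problems met during the intervention among the topics, and allows telephone and video. Whether there is an exit interview is the kind of detail a condensed article may leave to the full protocol. Feasibility is also judged on uptake, adherence and data completeness, and drop-out reasons are recorded. Because the interviews are analysed thematically, no acceptability rate exists that could be inflated.

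Most of this stands. Interviewing people who withdraw is not forbidden, and information on them is not limited to the drop-out reason. It is also right that no numerical bias can be claimed. It does not remove the point, because what is questioned is timing the article does state, in two places, and that timing works against reaching people who leave.

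Three stronger readings are tempting and are not supported.

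- **That retention is biased upward by the entry criterion.** The full sentence reads most naturally as a capacity criterion. It speaks of inability, not of an expectation of leaving. It cannot select on dislike of a device not yet used, and leaving for that reason still counts against retention. Retention among those enrolled is a valid planning figure for a later trial with the same criteria. Counting people who were never enrolled as losses would need numbers the article does not give.
- **That interviews are closed to drop-outs by design.** The text leaves this open.
- **That every missing voice would be a dissatisfied one.** Feasibility assessment itself anticipates hospitalisation, life-threatening events and death, which can end participation for other reasons.

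**Conclusion.** The point holds in a limited form. If the stated timing is followed, people who discontinue are likely to be missed, and the acceptability and device findings, which are part of the primary outcome, are liable to lean towards completers. This assumes that some participants withdraw, that they differ in their views from those who stay, and that no one approaches them outside the stated schedule. If any of these fails, there is no effect. Its size cannot be derived from the documents. With so small a sample, even a few missing interviews could remove a theme altogether.

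The ambiguity in the eligibility sentence is a secondary matter of clarity. It does not support a conclusion that the retention estimate is inflated.

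**What to change.** 1. Reword Data collection and Semi-structured interviews so that every enrolled participant, including anyone who withdraws, is invited to interview: at the time of withdrawal where they agree, otherwise after post-assessment.
2. Report how many completers and how many withdrawers were invited and interviewed, and present the themes for the two groups separately.
3. Repunctuate the eligibility sentence to show whether the cooperation clause applies only to people with mental impairment. If it applies to everyone, report the number excluded on that ground alongside the recruitment and retention rates. The criterion need not be removed.

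The cost is a short amendment and a few extra brief interviews, which the same researcher can do by telephone under the modes already allowed. Participants remain free to decline. The acceptability findings may turn out less favourable.

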### Data collection

Pre-intervention and post-intervention measures of PA, SB, self-efficacy, self-report habits and well-being will be completed by participants. Socio-demographic characteristics of OAs will be measured at baseline. A qualitative interview will also be conducted using a semi-structured interview guide after the post-assessment period to assess the acceptability of the intervention. Interviews will be conducted in Urdu or English, with those that are conducted in Urdu translated into English by the primary researcher who will conduct these interviews.

PA will be measured with a wrist-worn accelerometer (ActiGraph wGT9X Link+, Pensacola, Florida, USA). The ActiGraph is reliable^86 87^ and valid for use with OAs,^88 89^ people with mobility limitations^89^ and obese adults.^90^,^92^ To measure each OA’s PA, they will wear the device on their non-dominant wrist for 7 days during waking hours and will remove it during any water-related activities such as bathing or swimming.^93^,^95^

OAs will be given a log sheet and asked to keep track of the times the accelerometer was worn and was removed throughout the day, describing the timings and reasons for each removal.^94 96 97^ Moreover, each OA will receive instructions on how to attach and wear the device for 7 consecutive days. They will also be asked to maintain a sleep log, recording hours slept and waking and rising times. This approach is beneficial to differentiate between wear and non-wear time and it also encourages compliance by acting as a reminder.^98^,^100^ Accelerometer data will be processed using ActiLife V.6.8.0 with data captured in 60 s epochs with the low-frequency extension enabled. The downloaded data will be subjected to compliance and quality control checks, and log sheets will be assessed to check the accuracy of wear time algorithms and to remove the non-wear time from the study.^96^

Total SB will be self-reported using the Measure of Older Adults’ Sedentary Time (MOST),^101^ which has been validated via objectively assessed sedentary time. It is divided into seven domains: reading, using a computer, watching television, socialising with friends and family, time on transport vehicles, doing hobbies or other activities. MOST data will be summed across the seven activities to provide a combined score. While exact minimal clinically important difference (MCID) values for MOST are unavailable, there are relevant studies and reviews that offer insight into what constitutes a meaningful change in SB. These identify that a reduction of 30–60 min can be seen as a significant difference.^88102^,^104^. Self-efficacy for exercise will be measured using the Self-Efficacy for Exercise (SEE).^105^ This tool is used to measure self-efficacy for activity. The SEE is a self-report measure with five items assessing one’s degree of confidence in the ability to perform the activity. The score is the sum of the item responses; higher scores indicate greater self-efficacy. There is no established MCID for SEE^106^; however, for the present study, the Minimal Important Difference (MID) will be estimated at around 1 to 2 points on the scale.^107^ The Self-Report Habit Index (SRHI)^37 108^ will be used to measure habits associated with SB (ie, sitting) and PA, which has been validated in previous studies.^109 110^ The MCID for the SRHI is not as widely established as for some other scales. However, research suggests that a change of about 0.5 to 1 point on the SRHI scale represents an MID. The Warwick-Edinburgh Mental Well-being Scale,^111^ a 14-item self-report measure, will be used to assess well-being. Respondents rate their experience regarding each statement over the last 2 weeks. Each item is scored using a 5-point Likert scale ranging from 1 (none of the time) to 5 (all of the time), with the total score ranging from 14 (low well-being) to 70, and the MCID is represented by a change of three points.^112 113^

### Feasibility assessment

The primary outcome is the acceptability and feasibility of the procedures of the intervention and recruitment and retention measurement. Recruitment rates were determined as the ratio of study participants who consented to participate out of those invited and eligible to participate. We will assess the attendance at, and time taken (minutes) for, the face-to-face health coaching session. Similarly, we will note the number of sent and successfully delivered messages and record the number of responses to, and acknowledgements of, the messages. Further, weekly reading/usage of the pamphlet will be recorded. We will use qualitative interviews to determine their overall user experience with the intervention which will help us to assess device feasibility by examining their perception regarding the vibrations and sound messages emitted from the device.

In addition, we will record drop-out reasons for discontinuing study participants, as well as adverse events experienced (eg, hospitalisation, life-threatening events, death). The suitability of measurement procedures will be evaluated based on the completion rates of the measures.

### Semi-structured interviews

Following the completion of the intervention, semi-structured interviews will be conducted with enrolled OAs who participated in the trial to understand the intervention’s feasibility and acceptability. The interview guide is based on the UK MRC framework. A key component in planning health-associated interventions is the feasibility phase, which produces important information on areas such as acceptability, usability and functionality that will be assessed using the interview guide (online supplemental file 2).

Interviews will be held either face-to-face or via telephone, Zoom or any other appropriate interface to which the participants have access and will be conducted by the primary researcher ([name]). Enrolled OAs will be interviewed to explore information about the participants’ overall experiences (acceptability, usability and functionality) of using the multi-component intervention and its impact on their PA and SB, any problems they encountered during the intervention and how they feel it could be improved. All interviews are expected to last between 40 and 60 min and will be audio-recorded to allow subsequent verbatim transcription. If interviews are conducted in Urdu, they will be translated into English by the primary researcher ([name]). The reporting of the study will be in accordance with the COREQ checklist to ensure transparent and comprehensive reporting of qualitative research. The checklist is appended in online supplemental file 3, detailing specific items related to the research team, study design and data analysis.

### Data analysis

The primary researcher is accountable for the initial data entry. Statistical analyses will be done in SPSS, V.17.0. The intervention feasibility will be assessed through uptake, adherence and data completeness. Changes from baseline to post-test data in sedentary time, PA, well-being, self-efficacy and self-reported habits will be measured using paired t-tests. Linear regression analysis will be used to assess the impact of socio-demographic (age, gender, ethnicity and socio-economic status) and home characteristics on PA and SB, with the significance level set at p value <0.05.

Qualitative data analysis of interview data will use a thematic analysis technique to identify the common themes regarding the feasibility of the trial. The first step will use a combination of both inductive and deductive analysis using an open coding technique to identify themes and codes that give insights regarding the feasibility of the intervention and a future effectiveness trial. Initial deductive codes will be determined by the MRC framework. Two researchers will analyse the data independently; they will then have a detailed conversation about the themes and subthemes until an agreement is reached. In the next step, the identified themes and subthemes will be interpreted using the study’s underpinning models and theories to enable deeper interpretation and explanation of the study findings. The quantitative and qualitative data will then be combined for interpretation and reporting. The integration of the data will provide knowledge about the feasibility of the intervention which will also assist us in guiding an effective trial in the future.

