
## Methods

### Study design overview

This study will employ a multi-methods design, generating quantitative data and using subsequent semi-structured interviews to produce qualitative data on OAs’ experiences of the intervention and procedures. This feasibility study will be carried out and reported in accordance with the Standard Protocol Items: Recommendations for Interventional Trial guidelines to ensure appropriateness of the reporting of the protocol^56^ (online supplemental file 1). The study will recruit approximately 20–25 OAs and is planned to be conducted between 1 January 2024 and 31 May 2024. This range of sample size is not based on statistical power but was an appropriate and practical sample for a feasibility study^57^ considering resource (time, money and effort) constraints. This sample size is similar to that used in other feasibility studies in previous studies of non-pharmacologic interventions that explored similar outcomes and led to further effectiveness trials.^31 36 49 50^

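### Significance-tested linear regression of PA and SB on at least five predictors in 20–25 participants cannot support claims about what influences either behaviour

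*Protocol article*

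**What the plan says.** The Data analysis section of the protocol article plans paired t-tests for change from baseline, and then states: "Linear regression analysis will be used to assess the impact of socio-demographic (age, gender, ethnicity and socio-economic status) and home characteristics". The outcomes of this regression are PA and SB, and the same sentence fixes the criterion for a finding: "with the significance level set at p value <0.05". It does not call the regression exploratory, cap the number of predictors, mention multiplicity, or say whether predictors enter together or singly. Nor does it say whether the modelled PA and SB values are baseline, post-test or change.

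On sample size, the Study design overview says "The study will recruit approximately 20–25 OAs" and adds: "This range of sample size is not based on statistical power". The study has a single arm. The Feasibility assessment section makes acceptability, feasibility, recruitment and retention the primary outcome, so the regression is secondary.

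**The concern.** Five named predictors are the minimum. Two of them, ethnicity and socio-economic status, are naturally categorical. Recruitment is deliberately multi-ethnic ("Different community organisations working with multi-ethnic OAs (eg, Asian community, African community) in Swansea will be contacted"), so one column for ethnicity is unlikely to be enough. Home characteristics is a plural term and may also mean several variables.

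Three problems follow, and they should be kept apart:

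- **Overfitting.** A joint model with this many coefficients in 20–25 people explains a sizeable share of variance by chance, and its coefficients are unstable.
- **Multiplicity.** Many coefficients over two outcomes, each tested at 0.05 with no stated adjustment, make a false positive somewhere quite likely.
- **Low power.** A real association of moderate size is more likely to be missed than found.

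At stake is the credibility of any statement that, say, ethnicity or socio-economic status has an impact on PA or SB, made on data that cannot distinguish such a finding from chance.

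**Working it through.** There is no figure of the plan's to reproduce: the article gives no effect size, standard deviation, power or drop-out rate.

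**Inputs from the article.** n = 20 to 25 (Study design overview); threshold 0.05, two-sided assumed (Data analysis); two outcomes, PA and SB; five named predictors.

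**Assumptions.** The number of coefficients p is not stated. I use p = 5 (one column per named predictor, the most lenient count for a joint model) and p = 8 (age 1, gender 1, ethnicity 2, socio-economic status 2, home 2). A medium effect is taken as f² = 0.15, equivalent to a partial R² of 0.15/1.15 = 0.13.

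**Step 1: participants per coefficient, n/p.**
- p = 5: 20/5 = 4.0; 25/5 = 5.0.
- p = 8: 20/8 = 2.5; 25/8 = 3.1.

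**Step 2: expected R² with no true association, p/(n−1).**
- p = 5: 5/19 = 0.26; 5/24 = 0.21.
- p = 8: 8/19 = 0.42; 8/24 = 0.33.

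For comparison, with one predictor per model: 1/19 = 0.05; 1/24 = 0.04.

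**Step 3: chance of at least one p<0.05 over both outcomes when nothing is associated.** If all tests were independent this would be 1 − 0.95^(2p): 0.40 for 10 tests (p = 5) and 0.56 for 16 tests (p = 8). Coefficients in one model share a residual variance, so the tests are not independent. Simulation with independent null outcomes gives lower values:
- p = 5: about 36–37%.
- p = 8: about 45–49%.

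If the two outcomes are correlated at −0.5, the p = 5 figure is 33–35%. Each single t-test keeps its 5% level; the inflation comes from the number of tests, not from overfitting.

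**Step 4: power for one coefficient.** Non-central F with 1 and n−p−1 degrees of freedom and non-centrality n × f² (20 × 0.15 = 3.0; 25 × 0.15 = 3.75).
- p = 5 (14 and 19 residual df): 36% and 45%.
- p = 8 (11 and 16 residual df): 35% and 44%.
- One predictor per model (18 and 23 residual df): 37% and 46%.

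Power hardly depends on p. It is low because n is small.

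**Step 5: effect of drop-out.** The article states no rate. An assumed 20% loss from 20 leaves 16. With p = 5, participants per coefficient fall to 16/5 = 3.2, the expected null R² rises to 5/15 = 0.33, and power falls to 29%.

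**Step 6: scale.** About 55 participants would be needed for 80% power on one coefficient at a partial R² of 0.13, roughly twice the planned sample.

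**The case against.** The strongest defence has four parts.

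1. *The regression is not the main analysis.* Feasibility is judged through uptake, adherence and data completeness, and nothing in the article ties a progression decision to a regression coefficient. This stands and limits the severity. A reader might infer that a chance predictor will decide who is targeted in the later trial. The article says only that integrated quantitative and qualitative data will help guide that trial, so that inference is not supported.

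2. *A joint model is not stated.* The text says linear regression, not multivariable regression. This stands in part: overfitting is conditional on joint entry. One-at-a-time models would remove it, but the multiplicity and the low power would remain.

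3. *The sample is openly not power-based.* True, and acceptable for a feasibility study. But this admission sits badly with a significance threshold on predictor effects; it argues for description rather than testing.

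4. *Details may sit in a fuller document.* Coding of predictors and the choice of baseline, post-test or change values are commonly left there, so I make no finding of their absence. The same applies to home characteristics. A reader might infer that these are never collected, because the article names no measure for them. But its account of baseline data is one unitemised line ("Socio-demographic characteristics of OAs will be measured at baseline"), which does not list age, gender, ethnicity or socio-economic status either. A home item may be on a form not shown, so this is not part of the point.

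**Conclusion.** The concern holds as a moderate-to-minor point about a secondary analysis. The article commits to testing at least five predictors of two outcomes at p<0.05 in 20–25 people, and that sample cannot support conclusions about impact.

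The overfitting figures rest on joint entry and on an assumed 5–8 coefficients. The 36–50% chance of a false positive rests on unadjusted testing of that many coefficients over two outcomes, taken as independent; it is somewhat lower if they are correlated. The 35–45% power rests on f² = 0.15 and no drop-out.

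It would go too far to say that the regression is certain to overfit, or that it undermines the study's feasibility conclusion. The entry method is not stated, and the feasibility outcomes do not use the regression.

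**What to change.** In the Data analysis section, remove the p<0.05 rule for the regression and the claim to assess impact. Then do one of the following:

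- **Drop the regression** and show individual and subgroup changes in PA and SB descriptively, for example paired plots with mean and range by gender and ethnic group.
- **Keep it, labelled exploratory and descriptive**, for one or two predictors named in advance, reporting estimates with 95% confidence intervals and making no significance claims.

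The change costs about one sentence of wording and no extra data. What is lost is an exploratory predictor test that this sample cannot support.
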